### Selection of trial participants

Since random selection of patients was not possible because of small sample sizes and the initial requirement that Test patients be selected from areas connected to the NBN, a **B**efore **A**fter Control **I**ntervention (BACI) design [22] was adopted that foregoes assumptions of normality. The BACI paired samples design provides greater control over confounding variables, increases the power of the study and improves the chances of finding a significant result with a smaller number of samples if the impact is relatively small.

The research protocol requires the recruitment of 75 participants at each of the five sites to achieve a total sample size of 375. Of these 125 are Test patients and 250 are Control patients. At each site 25 participants are allocated to the intervention, with 50 remaining control participants receiving normal care as per their site’s existing model of care.

Eligible candidates are identified primarily by searching the local hospital patient administration system (PAS) for patients who satisfy the eligibility criteria described in Table 1. Some candidates were also identified by site clinical staff familiar with their medical history. Typically between 250 and 300 eligible patients are identified by searching the hospital records of the major community hospital in the region. Candidates are eligible to participate in the study if they meet all inclusion and none of the exclusion criteria listed in Table 1 and become participants on the signing of informed consent in the presence of an independent witness.

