**Table 1 Tab1:** **Clinical criteria for eligibility**

Criteria	Type	Description
Age	Inclusion	50 years old and over at consent.
Cognitive capacity	Inclusion	Abbreviated Mental Test (AMT) [23] score >7.
Unplanned acute admissions	Inclusion	A rate of unplanned acute admission with the required principal diagnosis code(s) indicated below:
		a) ≥2 in the last 12 months, or
		b) ≥4 in the previous 5 years.
ICD-10-AM principal diagnosis code(s) for each unplanned acute admission	Inclusion	Code(s) for each unplanned acute admission indicate a diagnosis for one or more of the following chronic conditions:
		a) Chronic Obstructive Pulmonary Disease (J41 – J44, J47 and J20, with secondary diagnosis of J41-J44, J47),
		b) Coronary Artery Disease (I20 – I25),
		c) Hypertensive Diseases (I10 – I15, I11.9. Note: Hypertensive Heart Failure (I11.0) is included in Congestive Heart Failure),
		d) Congestive Heart Failure (I11.0, I50, J81),
		e) Diabetes (E10 - E14),
		f) Asthma (J45).
Unsuitable conditions	Exclusion	The study team considers the presence of the following conditions to be unsuitable for participation in the study:
		a) Any form of cancer,
		b) Any neuromuscular disease
		c) Any psychiatric conditions.
Care team	Inclusion	The eligible patients must be under the care of any of the following:
		a) General Practitioner
		b) Community Nurse
Care programs	Inclusion	Participation in one of the following government care programs:
		a) Commonwealth Chronic Disease Management
		b) Commonwealth Coordinated Veterans’ Care Program
		c) NSW Connected Care Program
Unsuitable care programs	Exclusion	Participation in one of the following government care programs:
		a) Commonwealth Extended Aged Care in the Home

For the purposes of our study unplanned admissions are all admissions other than:Admissions from the waiting list (including both the surgical list and the medical waiting list);Admissions listed as "regular same day planned admissions" which are admissions that are intended regular and planned same‒day admissions for an on‒going phase of treatment, such as renal dialysis or chemotherapy.

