Following the signing of a consent form and completion of the Entry Questionnaire, Test patients are connected to the internet and supplied with the TMC Telemonitoring system and trained on its use by the Project Officer (PO) at each site. Their vital signs and questionnaire responses are subsequently monitored on a daily basis by the Clinical Care Coordinator (CCC). On site visits and technical support as well as the obtaining of Consent and the administration of Exit questionnaires are the responsibility of the PO.

Control patients also complete the Entry questionnaire but otherwise continue to receive normal care. For each intervention participant, as many as six control candidates are automatically case matched on gender, age, chronic condition and Socio-Economic Indexes for Areas (SEIFA) [24]. On their consent the two closest matching control candidates commence as participants in the study. The remaining four candidates are held in reserve. Table 2 below demonstrates the case matching process.

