**Table 2 Tab2:** **Example of case matching of Control patients with Test patients**

Test/control	Age	Gender	Major diagnosis	Seifa ^1^ index for postcode	Strength of match (perfect match = 0)
Test	54	M	COPD	1023	
Control	56	M	COPD	1025	1.68^2^
Control	54	F	HD	1022	2.16^3^
Weights	0.2	1	1	0.16	

^1^SEIFA 2011 Socio-Economic Indexes for Areas [24]. SEIFA provides measures of socio-economic conditions by geographic area.

^2^|54-56| × 0.2 + 1 × 0 + 1 × 0 + |1023-1015| × 0.16 = 1.68.

^3^|54-54| × 0.2 + 1 × 1 + 1 × 1 + |1023-1022| × 0.16 = 2.16.

Generally, the closer the match the greater the likelihood of finding a significant result with a smaller number of samples if the impact is relatively small.

Ideally, as many as four matches are sought for each Test patient, and the closest match is then selected as the case matched control for that Test patient. In many cases only one acceptable match may be available.

Following a change of Government in Australia, the requirement to connect patients to the high speed National Broadband Network was removed and as consequence, approximately half of our trial patients will be connected to a variety of NBN, ADSL, ADSL2 and VDSL network services with a minimum level of service of 2Mbps download and 1Mbps upload. Those on the NBN service were guaranteed a download speed of 25Mbit/sec and an upload speed of 5Mbit/sec.

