### Data analysis

Data will be analysed using a range of conventional statistical methods used in bio-statistics as well as model based methods more commonly found in the scientific statistical literature.

The independent samples t-test is commonly used when two separate sets of independent, randomly selected and normally distributed samples are available, one from each of the two populations being compared. However as explained previously, our project design makes random selection of Test and Control patients impossible and the alternative Before and After Control Intervention (BACI) design was adopted [22]. This design involved the site PO selecting the test patient first and then selecting from the remaining eligible test patients the controls that best match each test patient in turn.

As a consequence statistical comparisons in this study can only be validly made on Test – Control matched pairs and tested using the paired samples or repeated measures t-tests. We expect to obtain data from 125 test patients and up to 250 control patients. When two or more matched Control patients are available their data is averaged.

Data will be routinely tested for normality and if not normal, the appropriate transform, often log functions, will be applied to normalise the data prior to applying paired samples or repeated measures t-tests. Baseline characteristics will be described for time intervals as mean ± SDs for continuous symmetrical variables and means and 95% Confidence Intervals (CI) for skewed data. When before intervention data are available on outcomes, then the differences between the test and their controls will be tested to examine if there are any differences in the before intervention period. This process will be examined visually by examining boxplots of the time stamped differences (e.g., differences between the respective monthly variables eg. hospital costs) between test and control patient outcome measures.

As is common in the life sciences our data may be lognormal when not zero and may contain numerous zero values. In these circumstances the data will be modelled using a lognormal distribution for positive values, together with an additional probability mass at zero. This type of distribution is commonly referred to as delta-lognormal. 95% Confidence limits are calculated according to the method of Zou, Taleban and Huo [37].

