 Log of cost plus one will be treated as normally distributed with log of the number of days in the month as the offset. Sometimes the square root transformation may be used to stabilise the variance. We are hoping there are not too many zero cost periods or zero counts. If this fails we will use the zero adjusted inverse Gaussian distribution for the model – fitting them using the **gamlss** (package in R) using random() for including random effects [40]. τ_k(i)_ is a random effect in the above model that is assumed to be normally distributed with mean zero and constant variance. The assumption in the previous dot point and the assumption for e_ijk_ in the model thus assumes that measurements made at the same time segments (e.g., on the same quarter) have the same correlation and homogeneous variances for all repeated measures. The above model treats the study as a fully-designed experiment with the appropriate randomisation. However, this is seldom the case because most impact studies are observational in nature. The assumption is that each measurement for the intervention patients is matched with a measurement for one or more control patients. This blocking is expected to control for the non-randomisation in the design. The complexity of this analysis can be greatly reduced by taking the differences between the Test and Control measurements The model above tests whether a significant change has occurred by testing the significance of the interaction term of the model for the before after indicator variables and the control-intervention indictor variable. For example if the coefficient for intervention patients and after intervention duration has lower insured costs that before the intervention after adjusting for controls, then the intervention has had a significant impact on costs. The random effects terms and random error term are assumed to be uncorrelated in time. The control patient is generally selected to control for all covariates. In this study this means that control patients should be identical to the intervention patient in terms of age, gender, SEIFA index and major comorbidities. The samples are selected over time (therefore they are time series rather than repeated measures made at the same time). So it may seem unlikely that the model errors will be independently distributed but hospital costs are measured a month apart and this should be enough to for the assumption of independence to be valid. The assumption that all repeated measures have the same variance is unlikely to be true. If the gamlss package is used then this change in variance can be accounted for. Although theoretically longitudinal data structures can be modelled by random effects in gamlss [40] but at present no computationally feasible implementation for large sample sizes and complex models exists. Assume that the trend in the response variable over time is approximately linear. This assumption is likely to be reasonable over the 5 year study period, but is unlikely to be true for longer time periods.

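### Controls are not matched on prior unplanned admissions or entry route, so an unequal route mix would make regression to the mean look like an effect, or hide one

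*Protocol article*

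**What the plan says.** Table 1 admits a patient by either of two routes: (a) "≥2 in the last 12 months", or "b) ≥4 in the previous 5 years". Both count unplanned acute admissions for the listed conditions. Table 5 lists the number of unscheduled admissions as an outcome, and Table 6 includes hospital admissions.

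Under Selection of trial participants, "as many as six control candidates are automatically case matched on gender, age, chronic condition and Socio-Economic Indexes for Areas (SEIFA"). Table 2 shows the score as a sum of four weighted terms; its second example reads "54-54| × 0.2 + 1 × 1 + 1 × 1 + |1023-1022| × 0.16 = 2.16". No term refers to admission history or entry route. The assumptions under Classical BACI designs and extensions say that "control patients should be identical to the intervention patient in terms of age, gender, SEIFA index and major comorbidities", and the article expects this blocking to deal with the lack of randomisation.

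On who becomes a test patient, Data analysis states: "This design involved the site PO selecting the test patient first". Controls are then taken from the eligible patients who remain. On identification, Selection of trial participants adds: "Some candidates were also identified by site clinical staff familiar with their medical history".

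The effect is tested as the before/after by control/intervention interaction in a model with slopes for each group and period, under the assumption: "Assume that the trend in the response variable over time is approximately linear".

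**The concern.** Patients who enter by route (a) are caught at a recent peak and will on average fall back without any treatment. Patients who qualify only by route (b) have had at most one qualifying admission in the last year and will on average rise again. A before/after by group contrast removes a stable difference in level between test patients and their controls. It does not remove a difference in rebound. The variable that drives the rebound is the one used for selection, and it is the one left out of the match.

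If the mix of routes differs, the contrast for admissions and for costs linked to them is biased. More route (a) patients among the tests would produce a false benefit; more among the controls would hide a true one. The linear trend matters because a spike in the last before year tilts the fitted line upward for route (a), and a quiet last year tilts it downward for route (b).

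**Working it through.** **The plan's own figure.** Table 2, second control: 0 × 0.2 + 1 × 1 + 1 × 1 + 1 × 0.16 = 2.16, as stated. The score therefore contains only age, gender, diagnosis and SEIFA. The article gives no figure for the bias examined here.

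**Inputs from the article.** The two entry routes (Table 1); four years of hospital data before enrolment (Data architecture); an intervention period of 6 to 18 months, taken here as one year (Classical BACI designs and extensions).

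**Assumptions, not in the article.** Each patient has a constant personal admission rate drawn from a gamma distribution, with population mean 0.5 to 1.0 a year and shape 0.7 to 1.5. Yearly counts are Poisson and there is no treatment effect. The contrast is computed on annual counts, not on the transformed monthly scale.

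**Step 1, expected admissions by route (simulation, four corners of the grid).**

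| Mean, shape | Route (a): last 12 months → next year | Route (b) only: last 12 months → next year | False contrast per 10 points, trend extrapolated | Same, flat 4-year mean |
|---|---|---|---|---|
| 0.5, 0.7 | 2.63 → 1.38 | 0.58 → 1.03 | −0.17 | −0.02 |
| 0.5, 1.5 | 2.40 → 0.98 | 0.56 → 0.86 | −0.17 | −0.02 |
| 1.0, 0.7 | 3.23 → 2.31 | 0.60 → 1.31 | −0.16 | −0.02 |
| 1.0, 1.5 | 2.81 → 1.73 | 0.60 → 1.22 | −0.17 | −0.025 |

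A negative sign means a false fall in the group with more route (a) patients.

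**Step 2, what the trend does.** Take three before years at level *u* and a last year at level *v*. The least-squares slope is 0.3(*v* − *u*) and the mean is *u* + 0.25(*v* − *u*). The prediction for the next year is the mean plus 2.5 slopes: *u* + 0.25(*v* − *u*) + 0.75(*v* − *u*) = *v*. Extrapolating one year ahead is therefore the same as using the last 12 months as the baseline.

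**Step 3, the contrast.** False contrast = (difference in route (a) share) × [(next − baseline) for route (a) minus (next − baseline) for route (b) only]. First row of the table, 10 points:
- Trend extrapolated: 0.10 × [(1.38 − 2.63) − (1.03 − 0.58)] = 0.10 × (−1.25 − 0.45) = −0.17.
- Flat four-year mean (1.70 for route (a), 1.14 for route (b) only): 0.10 × [(1.38 − 1.70) − (1.03 − 1.14)] = 0.10 × (−0.32 + 0.11) = −0.02.

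**Step 4, relative size.** With half the controls on route (a), the first row's after rate is (1.38 + 1.03)/2 = 1.205, and 0.17/1.205 = 14%. Over the grid, with 40 to 70% of controls on route (a), the extrapolated contrast is about 8 to 19% of the after rate. Against the flat mean it is 1 to 2%.

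**Step 5, the remedies.** With equal route shares the contrast is 0.00 in every setting. With a 10-point imbalance, leaving the qualifying 12 months out of the before period changes the extrapolated contrast from −0.16 to −0.17 to about +0.02 to +0.04. That is a large reduction, with a small remainder of opposite sign.

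**The case against.** The strongest reply is that the bias needs an imbalance that nobody has shown. Controls meet the same criteria and come from the same site's eligible pool, so with an equal mix regression to the mean cancels. This stands, and it makes the point conditional.

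A reader might infer that test patients are the more recent frequent attenders, because they are picked first and staff nominate some candidates. The article does not say so. The nomination sentence concerns candidates in general, and the stated restriction on test patients was the broadband area, later lifted. For the same reason it does not follow that the bias favours the intervention.

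Chance alone would rarely produce a large imbalance. With 125 test and 250 control patients and a route (a) share *p* of 50 to 80% (assumed), the standard error of the difference, ignoring pairing, is √[*p*(1 − *p*)(1/125 + 1/250)] = 4.4 to 5.5 points. Twenty points is then about 3.7 to 4.6 standard errors. A smaller chance imbalance is sampling variation rather than systematic bias.

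The size also depends on how the model is read. The article plans paired t-tests and an interaction test as well as slopes, and against a flat before mean the bias is small. But the article itself sets the standard BACI design aside for trending variables and adopts slopes, which is the version that enlarges the bias.

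Finally, differences in the before period will be tested and time-stamped differences plotted. That could reveal an unequal spike, and the response to it may be in an analysis plan that is not shown. The matching rule, however, is fixed in the article, and it is relied on to make up for the missing randomisation.

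**Conclusion.** The point holds in conditional form. The match omits the variable on which patients were selected, in a non-randomised design that leans on the match. If the route mix differs, each 10 points of imbalance shifts the contrast by about 0.16 to 0.17 admissions per patient-year when the linear before-trend is extrapolated, and by about 0.02 against a flat four-year mean. The sign follows the imbalance. These figures rest on the assumed gamma-Poisson model, four before years and one after year, on the count scale.

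Two stronger readings are not supported. One is that the selection variable is the trial's main outcome: the article names no primary outcome, and hospital admissions is one of ten measures in Table 6. The other is that this bias would account for an effect as large as the 20% fall in emergency admissions cited in the Background. At 8 to 19% per 10 points, that would need an imbalance of about 10 to 25 points (20/19 × 10 to 20/8 × 10) together with the extrapolated trend, and no such imbalance is documented.

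**What to change.** - Report entry route and unplanned admissions in the prior 12 months by arm.
- Adjust the BACI model for both, with their period interactions.
- Repeat the analysis with the qualifying 12 months left out of the before period, and read it beside the main result. It is a diagnostic and not a full correction, given the small remainder in Step 5.
- For patients still to be matched, add the prior 12-month count as a weighted term in the match score.

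The hospital search that establishes eligibility already yields these data. The cost is slightly looser matches on age or SEIFA and a little more analysis. Exact matching on route should not be forced: the text below Table 2 says that often only one acceptable match can be found, so an exact requirement could lose pairs.

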**Table 2 Tab2:** **Example of case matching of Control patients with Test patients**

Test/control	Age	Gender	Major diagnosis	Seifa ^1^ index for postcode	Strength of match (perfect match = 0)
Test	54	M	COPD	1023	
Control	56	M	COPD	1025	1.68^2^
Control	54	F	HD	1022	2.16^3^
Weights	0.2	1	1	0.16	

^1^SEIFA 2011 Socio-Economic Indexes for Areas [24]. SEIFA provides measures of socio-economic conditions by geographic area.

^2^|54-56| × 0.2 + 1 × 0 + 1 × 0 + |1023-1015| × 0.16 = 1.68.

^3^|54-54| × 0.2 + 1 × 1 + 1 × 1 + |1023-1022| × 0.16 = 2.16.

Generally, the closer the match the greater the likelihood of finding a significant result with a smaller number of samples if the impact is relatively small.

Ideally, as many as four matches are sought for each Test patient, and the closest match is then selected as the case matched control for that Test patient. In many cases only one acceptable match may be available.

Following a change of Government in Australia, the requirement to connect patients to the high speed National Broadband Network was removed and as consequence, approximately half of our trial patients will be connected to a variety of NBN, ADSL, ADSL2 and VDSL network services with a minimum level of service of 2Mbps download and 1Mbps upload. Those on the NBN service were guaranteed a download speed of 25Mbit/sec and an upload speed of 5Mbit/sec.

### Subject enrollment and consent

Eligible patients are initially contacted by the Trial PO and given a detailed information sheet outlining the project. Confirmation of willingness to participate is via a consent document witnessed by a person independent of the project. Upon consenting the patient is administered a comprehensive Point of Entry Questionnaire as described in Table 3 using OpenClinica [25], the world's first commercial open source clinical trial software for Electronic Data Capture (EDC) and Clinical Data Management (CDM), as the data depository and data management system. Processes are then put in place to connect the telemonitoring system and to train the patient on its use. A Quality Control process operates for one week to ensure that patient training is adequate and the quality of the data recorded is acceptable.

**Table 3 Tab3:** **Key elements of the Entry and Exit Questionnaires**

Section	Source/questionnaire
1-3	CSIRO Standard Screening Medical Questionnaire [29] + additional trial specific questions
	Selected questions from Living with Diabetes Study [30]
	Selected questions from Fat and Fibre Barometer [31]
4	Active Australia [32]
5	Kessler 10 [33]
6	Dimensions from HeiQ (Living with and managing medical conditions) [34]
7	EuroQol EQ-5D [35]
8	Dimensions from HeiQ (Social Isolation) [34]
9	Morisky Medication Adherence [36]

Once each Test patient is consented, an automated case matching process is carried out as already described.

### Selection of Tele-monitoring service provider

CSIRO undertook a comprehensive and independent Technology Assessment process to select the telehealth service provider for this project. The selection committee was chaired by the Leader of the Health Services Theme, and comprised six members including partner representatives.

From an initial review of companies operating in the Australia market, six were selected for further consideration based on length of presence in Australia and experience with supporting telehealth services in a trial environment. These were requested to provide detailed information on their at home tele-monitoring equipment and ultimately three were interviewed and asked to provide a physical demonstration of their equipment. Criteria for selection included the following;

Range of vital signs measurements available, patient Video conferencing and messaging capability, Clinical Questionnaires specific to patient condition, ability to view vital signs data in raw signal form, quality/ease of use of patient user interfaces, quality/ease of use of clinician user interfaces, expert system for daily patient risk profiling, high quality video for delivery of Educational/training material, multi language capability, quality standard and data accessibility, regulatory compliance (TGA, CE Mark, FDA, ISO13485), capability to export data from the system, opportunity to partner with the provider to trial new tools, algorithms and analytic results within their system, evidence of capability to deploy and service equipment in the field, including patient training, remote maintenance etc., availability of local R&D support, quality of support staff and management, evidence of experience in deploying telehealth services, cost of Equipment/Services and data storage location.

Based on a comparative analysis of the criteria identified above, Telemedcare Systems Pty Ltd [26] was selected as the telehealth service. Critical attributes identified were (i) meeting all TGA, FDA and CE Marking regulatory requirements, (ii) commercial presence in Australia since 2006 and proven track record in supporting telehealth projects in Australia and the UK, (iii) Local customer support and software and hardware R&D capability, (iv) advanced clinical capability including spirometry, ecg and auscultatory NIBP and strong local R&D support and (v) ability to view all recorded traces for purposes of improved diagnosis and quality control particularly in patients who may have cardiac arrhythmia.

The TMC Clinical Monitoring Unit (CMU) is shown in Figure 3. Not all features were necessarily used in this trial.

